# **12．Study implementation period**

July 15, 2017 to June 15, 2018 (Final enrollment date: May 15, 2018)

Enrollment period: 11 months. Study period: 12 months.

# **13. Subject analysis (sub-group for effectiveness evaluation) and method of statistical analysis (primary/secondary analysis)**

A summary of the planned statistical analysis of this study is provided below. Details of the planned statistical analysis will be described in the statistical analysis plan. The summary of the planned statistical analysis described in this protocol may be changed in the statistical analysis plan. If the definition or analysis method for the primary endpoint is changed, the protocol will be amended.

1. Analysis populations

（1） Full analysis set (FAS)

The full analysis set (FAS) will consist of all subjects enrolled in the study, who have efficacy data available, excluding those without baseline data or significant protocol violations (e.g., absence of informed consent, enrollment outside the contract period).

（2）Per protocol set (PPS)

The per protocol set (PPS) will consist of the subjects in the FAS excluding those with any of the following significant protocol violations involving the study method, concomitant therapy, etc.:

- violation of the inclusion criteria
- violation of the exclusion criteria
- violation of prohibited concomitant medications
- violation of prohibited concomitant therapies

（3）Safety analysis set

The safety analysis set will consist of the subjects enrolled in this study who received any UV irradiation.

2．Target sample size and rationale

Target sample size: 20

This exploratory study will be conducted to gather information to properly design new clinical trials with patients. For this reason, the target number of cases was set in order to collect a wide range of efficacy and safety indicators. Theoretically, it is assumed that the possibility that 222 nm UVC will not cause erythema in the irradiated area is almost 100%. It is thought that this irradiation method will be judged to be appropriately safe when the one-sided 95% confidence interval lower limit is higher than 75%. In this study, the number of enrollment subjects will be gradually increased from 2 subjects to 20 subjects in total. If erythema does not appear in all 20 participants, the one-sided 95% confidence interval lower limit will be 83.9%. Since this test will be conducted as an exploratory one, when considering the implementation of the next phase of the test, the primary and secondary evaluation items will be comprehensively judged.

3．Items and plan of the statistical analysis

The analysis will be performed after the completion of UV irradiation and sampling in all subjects. For all efficacy endpoints, the FAS will be used in the primary analysis, while the PPS will be used in a reference analysis. Safety will be analyzed using the safety analysis set.

(1) Safety analysis

1) Presence or absence of erythema

The erythema non-occurrence rate and its 95% confidence interval for each dose will be calculated.

2) Examination of DNA damage

The amount of CPD produced in the UV irradiation group and non-irradiation group will be compared using a paired *t*-test. If the amount of CPD produced is significantly higher in the irradiated group than in the non-irradiated group, it will be determined that there is DNA damage due to UV irradiation. The hypothesis testing will use a significance level of two-sided 5%, with the calculation of the two-sided 95% confidence interval.

3) Frequency of adverse events

A summary table will be prepared for the endpoint. For estimation of the proportion, the exact two-sided 95% confidence interval for a binomial distribution will be calculated per group. As necessary, Fisher’s exact test will be used for inter-group comparison.

(2) Efficacy analysis

1) Primary analysis

Bacterial detection frequency from skin swabs will be compared using the Χ^2^ test. The hypothesis testing will use a significance level of two-sided 5%, with the calculation of the two-sided 95% confidence interval.

2) Secondary analysis

The secondary efficacy endpoints will be analyzed for discussion to supplement the primary analysis results. No multiplicity adjustment will be performed in the analysis of secondary efficacy endpoints. The hypothesis testing will use a significance level of two-sided 5%, with the calculation of the two-sided 95% confidence interval.

(3) Interim analysis

No interim analysis is planned in this study.

(4) Independent data monitoring committee (IDMC)

An IDMC will not be established in this study.

(5) Final analysis

The final analysis will be performed after data from the subjects have been obtained and locked after the end of the follow-up period. The responsible biostatistician will prepare the “statistical analysis report” and submit it to the principal investigator.

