# **7．Endpoints**

1）Primary endpoint
・Presence or absence of skin erythema at 24 hours after UV irradiation with 500 mJ/cm^2^ 222 nm UVC or less.

2）Secondary endpoints

1. Bactericidal effect of skin indigenous bacteria by UV irradiation.

2. DNA damage in skin cells after UV irradiation.

3. Adverse events.

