# **8．Survey items**

（1）Observation and inspection items to be collected during the test

1) At the time of informed consent

- The identification code of the subject will be confirmed, gender, date of birth, height, weight, complications, and medical history will be checked, and study eligibility will be assessed.

＜Step 1＞

2) Before irradiation

- Specify the irradiation range of six places (E1, E2, E3, E4, E5, E6. 10 x 10 mm each.) on the back of the subject. Since the irradiation dose does not depend on the irradiated area, it is not necessary to set a strict size of the area. Specify the range (N, 10 x 10 mm) on the subject's back where UV is not irradiated. (Figure 6)

3) UV Irradiation

- Doses of 50, 100, and 200 mJ/cm^2^ 222 nm UVC will be irradiated onto E1, E2, and E3, respectively. The amount of irradiation can be measured with the irradiation equipment itself. The time required for irradiation is approximately 10 seconds at 50 mJ/cm^2^, approximately 20 seconds at 100 mJ/cm^2^, and approximately 40 seconds at 200 mJ/cm^2^. (Figure 6）

Figure 6. Irradiated area and irradiation doses ①

|  | UVC (+) 50 mJ/cm^2^ | UVC (+) 100 mJ/cm^2^ | UVC (+) 200 mJ/cm^2^ | UVC (-) |
| --- | --- | --- | --- | --- |
| Erythema | **E1** | **E2** | **E3** | **N** |

4) 24 hours after irradiation

- The presence or absence of erythema in E1, E2, and E3 will be evaluated and compared with N. A photograph of the non-irradiated and irradiated area will be retained. If no erythema is observed after 24 hours, proceed to step 5 (next). If erythema is observed, the minimum dose that causes erythema will be taken as the minimum erythema dose (MED), and the UVC dose in step 2 will be determined as in Figure 8.

5) UV irradiation

- Doses of 300, 400, and 500 mJ/cm^2^ of 222 nm UVC will be irradiated onto E4, E5, and E6, respectively. The time required for irradiation is approximately 60 seconds at 300 mJ/cm^2^, approximately 80 seconds at 400 mJ/cm^2^, and approximately 100 seconds at 500 mJ/cm^2^. (Figure 7)

Figure 7. Irradiated area and irradiation doses ②

|  | UVC (+) 300 mJ/cm^2^ | UVC (+) 400 mJ/cm^2^ | UVC (+) 500 mJ/cm^2^ | UVC (-) |
| --- | --- | --- | --- | --- |
| Erythema | **E4** | **E5** | **E6** | **N** |

6) 24 hours after the irradiation

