# **11．Completion, termination, and suspension of the trial**

・Criteria for discontinuation or suspension of the study

1. Case registration will be suspended if any serious adverse event that could lead to death or mortality and that a relationship with UV irradiation cannot be denied is observed.
2. If any erythema is observed after 50 mJ/cm^2^ UV irradiation in the first step of this study (8. (1)), the study will be discontinued.
3. When any of the following information is obtained, the principal investigator will decide discontinuation or suspension of the entire study based on the judgement by the principal investigator or discussion with the head of the research institution. If the ethical committee instructs to cancel or suspend the study, investigators will follow the instructions promptly.

1) When there is a problem with the safety and effectiveness of UV irradiation.

2) When there is a problem with the safety or effectiveness of the protocol treatment.

3) When there is a cancellation recommendation from the regulatory authority.

4) When there is a change in the development policy of the principal investigator.

5) When other situations arise that require some or all of the study to be discontinued or suspended.

・Procedures for discontinuing or suspending the entire study

1. When the study at a research institution is discontinued or suspended, the principal investigator will promptly notify the fact of discontinuation/suspension to the study subjects and guarantee appropriate procedures such as switching to an appropriate treatment.
2. When the study at a research institution is discontinued or suspended, the principal investigator will promptly notify this to the head of the research institution in writing.
3. When the principal investigator has decided discontinuation or suspension of the study, the principal investigator will notify the details of that and the reason in writing to the head of the research institution.

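### Erythema rates at 300–500 mJ/cm² exclude subjects who already reacted at 100 or 200, so they overstate safety, and the 75% criterion is not tied to a rate that avoids this

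*Protocol*

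**What the plan says.** **Endpoint.** Section 7 of the protocol gives the primary endpoint as "Presence or absence of skin erythema at 24 hours after UV irradiation with 500 mJ/cm^2^ 222 nm UVC or less".

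**Procedure.** In Section 8 (1), Step 1, each subject first receives 50, 100 and 200 mJ/cm² on three separate sites. At 24 hours the rule is "If no erythema is observed after 24 hours, proceed to step 5 (next"), where item 5 is the high-dose block: "Doses of 300, 400, and 500 mJ/cm^2^ of 222 nm UVC will be irradiated onto E4, E5, and E6, respectively". For a subject who has reacted, the text says "If erythema is observed, the minimum dose that causes erythema will be taken as the minimum erythema dose (MED"), and nothing sends that subject on to the high doses. The gate works subject by subject, because Step 2 waits until the MED has been determined for all 20.

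**Stopping at 50.** Section 11 discontinues the study in this case: "If any erythema is observed after 50 mJ/cm^2^ UV irradiation in the first step of this study". Section 4 has the same rule.

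**Analysis.** Section 13, item 3 (1) 1) reads "The erythema non-occurrence rate and its 95% confidence interval for each dose will be calculated". No denominator is given. The population for safety is set in item 1 (3): "The safety analysis set will consist of the subjects enrolled in this study who received any UV irradiation".

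**Criterion.** Section 13, item 2 judges the irradiation method appropriately safe if the lower limit of a one-sided 95% interval for non-occurrence is above 75%. Its illustration is no erythema in any of 20 participants, with a stated limit of 83.9%. No dose is named.

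**The concern.** Whether a subject has a result at 300, 400 or 500 depends on the outcome being measured. Subjects sensitive enough to react at 100 or 200 are, by design, never observed at the higher doses. A rate at 500 among those irradiated at 500 therefore estimates non-occurrence in people already shown not to react at 200. It does not estimate non-occurrence in the healthy volunteers who entered.

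The endpoint (erythema at 500 or less) and the sample-size illustration (all 20 participants) both describe a subject-level, cumulative quantity. The planned analysis is a set of separate per-dose rates, and nothing links the 75% criterion to any of them. What is at stake is the figure quoted for the highest dose, and a safety conclusion meant to inform the design of later trials in patients.

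**Working it through.** **Inputs.** From the protocol: N = 20; criterion of a one-sided 95% lower limit above 75%; two blocks, 50/100/200 then 300/400/500, with the gate between them. Assumed, because the protocol gives no figures: the number of early reactors, and the share of all reactors who react at 100–200.

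**The plan's own figure.** For 20/20, the Wilson limit with z = 1.96 is 20/(20 + 1.96²) = 20/23.84 = 83.9%, which reproduces the stated value. That is the lower end of a two-sided 95% interval. The exact one-sided 95% limit is 0.05^(1/20) = 86.1%. The label does not affect this point, and both methods are shown below.

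**Method.** The exact one-sided 95% lower limit for x of n is the 5% quantile of Beta(x, n − x + 1), which is 0.05^(1/n) when x = n. Let k subjects react at 100 or 200 and none of the other 20 − k react at 300–500. Compare the rate at 500 among those irradiated, (20 − k)/(20 − k), with the rate over all subjects, (20 − k)/20.

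| k | Irradiated at 500 | Exact limit | All subjects | Exact limit | Criterion: irradiated / all |
|---|---|---|---|---|---|
| 1 | 19/19 | 85.4% | 19/20 | 78.4% | met / met |
| 2 | 18/18 | 84.7% | 18/20 | 71.7% | met / not met |
| 3 | 17/17 | 83.8% | 17/20 | 65.6% | met / not met |
| 5 | 15/15 | 81.9% | 15/20 | 54.4% | met / not met |
| 9 | 11/11 | 76.2% | 11/20 | 34.7% | met / not met |
| 10 | 10/10 | 74.1% | 10/20 | 30.2% | not met / not met |

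The two disagree for k = 2 to 9. With the two-sided Wilson limit they disagree for k = 2 to 8; at k = 2 the limits are 82.4% and 69.9%. One early and one late reactor also separate them: 18/19 gives 77.4% and 18/20 gives 71.7% (exact).

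**Chance of meeting the criterion.** Suppose the true cumulative non-occurrence rate up to 500 is 75%, the boundary. Over all 20 subjects the exact rule needs at least 19/20, and 0.75^20 + 20 × 0.25 × 0.75^19 = 0.32% + 2.11% = 2.4%. Among subjects irradiated at 500, enumerating early and late reactors gives:

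| Assumed share of reactors reacting at 100–200 | Chance of meeting the criterion at 500 |
|---|---|
| 0% | 2.4% |
| 50% | 16% |
| 80% | 43% |
| 100% | 98.6% |

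**What the lower-dose rows would show.** Everyone receives 100 and 200, so those rows keep 20 in the denominator. With k = 3 the 200 row is at best 17/20 if the three reactions were all seen at 200, limit 65.6%. In the 80% scenario, 20% of subjects react at 100–200; if they all show at 200, that row meets the criterion with probability 0.8^20 + 20 × 0.2 × 0.8^19 = 1.2% + 5.8% = 6.9%. Requiring both the 200 and 500 rows to pass would then succeed at most 6.9% of the time, against 43% for the 500 row alone.

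**The case against.** The other side has a good case, and much of it stands.

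- **The denominator is not stated**, and Section 13 leaves details to the statistical analysis plan. True. But the protocol fixes a per-dose rate for its primary endpoint, and the same section requires an amendment if the definition or analysis of that endpoint changes. A rate for each dose is naturally read as being among those who received the dose.
- **The criterion is never assigned to the 500 row.** This stands. A reader might infer that the plan will declare safety on the 500 rate alone. The document does not say so; its only illustration uses all 20 participants, which is close to the fix below.
- **The early reactors stay visible** in the 100 and 200 rows. This stands, so the distortion is not hidden from someone who reads the whole table.
- **Dose selection is untouched.** This stands: Step 2 follows the lowest MED over all subjects, whatever the 500 rate is, and Section 13 promises an overall judgement across endpoints.
- **Erythema is expected almost never.** A change of verdict needs at least two reactors, one of them early. If 2% of subjects react (an assumption), the chance of two or more among 20 is about 6%. But Section 3 accepts that skin damage has not been ruled out, and Section 6 counts a barely visible change seen by one physician as positive.

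Two further inferences go too far. A reader might suppose that untreated sites would be counted as free of erythema because the safety set includes anyone irradiated; no sentence says that. A reader might also include reactors at 50 among those lost to the higher doses; erythema there discontinues the study, so only 100 and 200 matter.

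**Conclusion.** The point holds in limited form. With the Step 1 gate, the planned rates at 300, 400 and 500 mJ/cm² are conditional on no reaction at 50–200 and, on the natural reading of the denominator, overstate safety whenever anyone reacts at 100 or 200. If the 75% criterion is applied to the 500 rate, it can be met where the all-subject rate fails, from two early reactors upwards. At a true cumulative rate of 75%, the chance of meeting it rises from 2.4% to between 16% and 98.6% when half to all of the reactors react early. Those shares are assumptions.

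With no reactor or one, the criterion is met either way. The harm is confined to the reported high-dose rates and the overall safety conclusion drawn from them.

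**What to change.** In Section 13, item 3 (1) 1), define the non-occurrence rate at dose d as the proportion of all irradiated subjects with no erythema at any dose up to and including d, so that a subject positive at one dose counts as positive at every higher dose. State that the 75% criterion applies to this cumulative rate up to 500 mJ/cm². Observed per-dose rates can be shown alongside, each with its actual denominator.

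The change is to the analysis only; no irradiation procedure alters. It takes a sentence or two, but since it concerns the primary endpoint it belongs in a protocol amendment. The criterion would then need 19/20 or 20/20. If the true rate is 99% (an assumption in line with the protocol's expectation of almost 100%), that happens with probability 0.99^20 + 20 × 0.01 × 0.99^19 = 98.3%, so little is lost. The downside is an assumed monotone dose response, which the MED rule already implies; a false positive call at a low dose would also be carried upwards.

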# **4．Subjects**

Those who meet all of the following inclusion criteria and do not fall under any of the following exclusion criteria are the subjects of this study.

1. Inclusion criteria：

1）Those who are between 20 and 80 years old at the time of obtaining consent.

2）Gender: both female and male.

3）Those who provided documented consent by their voluntary intention to participate in this trial.

2）Exclusion criteria：

1) Sensitivity to drugs, such as allergies.

2) Abnormality at the site of UVC irradiation on the back, such as dermatitis or trauma.

3) Regular use of topical medication or patches at the site of UVC irradiation on the back.

4) Tattoos at the site of UVC irradiation on the back.

5) Pregnancy, the possibility of pregnancy or breast-feeding.

6) Participation in other clinical trials within four months.

7) Rejection as inappropriate for participation by the physician in charge of the clinical trial.

Rationale:

2) Set to ensure the safety of subjects.

4) Set because there is a possibility of hindering the evaluation of changes by UV irradiation.

5) Set because the safety of the equipment for pregnant women and fetuses has not been confirmed.

6) Set in consideration of ethical issues for subjects participating in clinical trials.

7) Set to leave room for the investigator to decide whether or not the subject can participate in this study, taking into account all other factors than those mentioned above and ensuring the safety of the subjects.

3）Target sample size:

20

4）Procedure of enrolling subjects:

To ensure safety, UV irradiation will be performed on two subjects and they will be checked for the presence or absence of erythema 24 hours after irradiation. If there is no situation where erythema appears with an irradiation dose of 50 mJ/cm^2^, which is the minimum irradiation dose, the number of patients enrolled in stages will be increased. Four subjects first, followed by six and eight subjects. (<Step 1> in 8. (1) shown below) If erythema appears in a subject after irradiation at 50 mJ/cm^2^, the study will be discontinued.

After 20 subjects have been enrolled, the following <Step 2> shown below as 8. (1) will be performed.

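### The per-dose erythema rates at 300, 400 and 500 mJ/cm² come only from subjects who did not react at the lower doses, and overstate non-occurrence if anyone reacts at 100 or 200

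*Protocol*

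**What the plan says.** Step 1 (Protocol section 8 (1)) has two blocks on each subject's back. In the first, "Doses of 50, 100, and 200 mJ/cm^2^ 222 nm UVC will be irradiated onto E1, E2, and E3, respectively". After the 24-hour reading: "If no erythema is observed after 24 hours, proceed to step 5 (next" (that is, item 5 of the list). Otherwise: "If erythema is observed, the minimum dose that causes erythema will be taken as the minimum erythema dose (MED"), and the text does not send that subject on. In the second block, "Doses of 300, 400, and 500 mJ/cm^2^ of 222 nm UVC will be irradiated onto E4, E5, and E6, respectively", with no gate between these three doses. Section 4 adds a stop for the whole study: "If erythema appears in a subject after irradiation at 50 mJ/cm^2^, the study will be discontinued".

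The primary endpoint in section 7 is "Presence or absence of skin erythema at 24 hours after UV irradiation" at 500 mJ/cm² or less. Its analysis, in section 13 item 3 (1) 1), is one sentence: "The erythema non-occurrence rate and its 95% confidence interval for each dose will be calculated". Safety is analysed in a population that is not dose-specific: "The safety analysis set will consist of the subjects enrolled in this study who received any UV irradiation". No denominator is given for 300, 400 or 500, and no rule for a subject who was not irradiated there because of an earlier reaction.

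Section 13 item 2 would judge the irradiation method appropriately safe if a one-sided 95% lower limit exceeds 75%. It quotes 83.9% for 20 of 20 without erythema.

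**The concern.** Whether a subject has a reading at 300 to 500 depends on the outcome being measured. The subjects missing there are those already known to react at a lower dose. A simple proportion among those irradiated therefore describes a selected, less sensitive group, and its confidence interval covers the conditional rate, not the rate in all subjects.

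The error is always towards safety, and it grows with the number of early reactors. The printed table could show non-occurrence rising with dose. That is at odds with the protocol's own use of the MED as a threshold. A reader planning the next trial could take the figure at 500 as the rate in healthy volunteers generally.

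**Working it through.** **Inputs.** From the protocol: n = 20; first block 50/100/200; second block 300/400/500 only after a clear first block; 75% mark; stated limit 83.9%. The protocol gives no reaction probabilities beyond an expectation of almost 100% non-occurrence, so the probabilities in step 3 are assumptions.

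**1. The plan's own figure.** For n of n without erythema, the Wilson lower limit is n/(n + z²). With z = 1.96, 20/(20 + 3.8415) = 83.9%, which matches. This is the lower end of a two-sided 95% Wilson interval. The exact one-sided 95% limit is 0.05^(1/20) = 86.1%. The one-sided label is a separate matter; the comparison below does not depend on it.

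**2. Effect of k early reactors.** Let k subjects react at 100 or 200 and nobody react later. (A reaction at 50 ends the study, so selection works only through 100 and 200.) The exact one-sided 95% lower limit is 0.05^(1/n) for n/n, and otherwise the 5th percentile of Beta(x, n − x + 1).

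| k | Irradiated only at 500 | Lower limit | Reactors carried forward | Lower limit |
|---|---|---|---|---|
| 0 | 20/20 = 100% | 86.1% | 20/20 = 100% | 86.1% |
| 1 | 19/19 = 100% | 85.4% | 19/20 = 95% | 78.4% |
| 2 | 18/18 = 100% | 84.7% | 18/20 = 90% | 71.7% |
| 3 | 17/17 = 100% | 83.8% | 17/20 = 85% | 65.6% |

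From k = 2 the two limits lie on opposite sides of 75%. The two-sided Wilson method behind the stated 83.9% gives the same reversal at k = 2: 82.4% against 69.9%. If one further subject reacts at 500, k = 1 is enough: 18/19 has limit 77.4%, 18/20 has 71.7%.

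If both reactors in the k = 2 row reacted at 200 and not at 100, the printed rates would be 18/20 = 90% at 200 and 18/18 = 100% at 300, 400 and 500.

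**3. What the irradiated-only rate estimates.** Let a be the probability of a first reaction at 200 or below and b that of a first reaction at 300 to 500. The rate in all subjects at 500 is 1 − a − b. The irradiated-only rate targets (1 − a − b)/(1 − a).

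| a | b | All subjects | Irradiated only | Difference (points) |
|---|---|---|---|---|
| 0% | 5% | 95.0% | 95.0% | 0 |
| 5% | 5% | 90.0% | 94.7% | +4.7 |
| 10% | 5% | 85.0% | 94.4% | +9.4 |
| 10% | 10% | 80.0% | 88.9% | +8.9 |
| 20% | 10% | 70.0% | 87.5% | +17.5 |

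The chance that at least one of 20 subjects is stopped early is 1 − (1 − a)^20: 64.2% for a = 5% and 87.8% for a = 10%. The three second-block doses are given together, so no further selection arises among them.

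**The case against.** The strongest reply is that nothing is decided on these rates. Section 8 (1) item 7 (Figure 8) sets the Step 2 dose from the lowest MED in all subjects. Section 6 item 4 sets the dose for a following study as the highest at which erythema does not appear. A reader might infer that an inflated rate at 500 would carry 500 forward. The documents do not support that: in the k = 2 example Figure 8 looks at the two reactors at 200, whatever is printed for 500. This part stands and limits the harm to reporting and interpretation.

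Nor does section 13 tie the 75% mark to the 500 rate. It attaches it to the irradiation method and illustrates it with all 20 participants. The endpoint can also be read per subject, as any erythema up to 500, and then an early reactor is simply positive and the gate removes nobody. So the reversal in step 2 is conditional: it happens only if someone holds the irradiated-only rate against 75%.

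A reader might also infer from the safety analysis set that a subject never irradiated at 500 would be counted as clear there, giving 20/20. Nothing in the protocol says so; naming a population does not assign outcomes to doses that were not given.

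The last reply is that section 13 is a summary and the statistical analysis plan, not available here, may settle the denominator. It may. But this sentence is the stated analysis of the primary endpoint, and section 13 itself requires a protocol amendment if that method changes. Taken at its natural meaning, the sentence gives a conditional rate without saying so.

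**Conclusion.** The point holds for the rates at 300, 400 and 500 as computed among irradiated subjects. They are conditional on no reaction at 200 or below and overstate non-occurrence in all subjects if anyone reacts at 100 or 200. With two such reactors and none later, 100% (lower limit 84.7%) would be reported at 500 in place of 90% (71.7%). Under the assumed probabilities above, the expected overstatement ranges from 0 to 17.5 points.

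This rests on a monotone dose response, which the MED rule and Figure 8 already presuppose. If non-occurrence is as near 100% as the protocol expects and nobody reacts in the first block, the bias is zero. Dose selection is not affected. Severity is moderate: a flaw in how the primary endpoint would be reported, cheap to remove, in an exploratory study whose endpoints are to be judged together.

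**What to change.** In section 13 item 3 (1) 1), define the estimator: the non-occurrence rate at dose d is the proportion of all subjects with an evaluable Step 1 reading whose MED exceeds d. Erythema at a lower dose counts as erythema at every higher dose, and a subject clear through 500 counts as exceeding every dose. Use exact binomial limits. Say separately how a subject with a clear first block but no second-block reading for another reason is handled, since that MED is known only to exceed 200. Report the irradiated-only rates at 300 to 500 as descriptive, labelled as conditional on no reaction in the first block, with their denominators.

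The rate at 500 then equals the per-subject reading of the primary endpoint.

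Cost: a few sentences, no new data and no change to what subjects receive, because the MED is already recorded. It makes the monotone assumption explicit, and the high-dose rates become less favourable if anyone reacts early. Since it concerns the primary endpoint, it should be settled by amendment before the Step 1 results are read.
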